### **b. Modification or interruption of the intervention**

During the implementation of this study, the intervention will be interrupted for each participant who presents (12):

- Withdrawal of informed consent;
- Discontinuation of treatment;
- Lost view ;
- Failure to process.

Chart 3 : Criteria for leaving the study outside of the cure

| Criteria                                        | Definition                                                                                                                                                       |
|-------------------------------------------------|------------------------------------------------------------------------------------------------------------------------------------------------------------------|
| Abandonment-confirmed                           | Patient absent for two consecutive weeks (declared abandonment in the third) sought by the RECOs and confirmed as having abandoned                               |
| Unconfirmed abandonment                         | Patient absent for two consecutive weeks (declared abandonment in the third) but his actual method of discharge (abandonment or death) not having been confirmed |
| Death                                           | Participant whose death has been certified by a nursing staff                                                                                                    |
| Lost view                                       | Change of address, followed in another CS outside the study area                                                                                                 |
| Treatment failure                               | Referred to UNTI following the appearance of danger signs (temporary discharge *)                                                                                |
| Withdrawal of consent                           | Any time after randomization                                                                                                                                     |
| Non-response to treatment (even if very rarely) | Children who do not recover after 12 weeks of treatment                                                                                                          |

*\*AT their return the children of the arm with reduced dose will resume with the dose planned for the week in which they were transferred, so they do not restart the treatment from zero but continue it.*

### c. Strategies to improve protocol adherence

Every evening, the principal investigator, the ACF Research RP and the three data collectors check all the data collected in the field in the different UNTAs. Inconsistencies, outliers or missing information for certain variables are noted and communicated to ACF supervisors who follow up within 24 hours and strengthen the capacities of UNTA agents, and also to RECOs. During their visit to enter data, data entry clerks also communicate certain weaknesses observed to healthcare providers with a view to correcting the data as far as possible.

In some cases where trained providers have moved or left their posts, other providers will be trained by the research team to ensure the continuity of the study.

For each child who does not respond to an appointment, RECO makes a home visit to find out what is going on.

#### d. Systematic treatment (Relevant concomitant care and interventions)

All children admitted to the study, regardless of their group, will receive systematic medical treatment as shown in the table below:

Chart 4 : Medical treatment of children admitted to the study

| Medications                                                                                | Weight (kg)    | Dosage (mg)       | Number caps / tab (250 mg) |
|--------------------------------------------------------------------------------------------|----------------|-------------------|----------------------------|
| Amoxicillin (50-100 mg / kg / day) for 7 days on admission
Dosage: 2 times a day | <5             | 125 mg * 2        | 1/2 cap * 2                |
|                                                                                            | 05 to 10       | 250 mg * 2        | 1 cap * 2                  |
|                                                                                            | 10 to 20       | 500 mg * 2        | 2 cap * 2                  |
|                                                                                            | 20 to 35       | 750 mg * 2        | 3 cap * 2                  |
|                                                                                            | > 35           | 1000 mg * 2       | 4 cap * 2                  |
| Medications                                                                                | Age            | Dosage            |                            |
| Albendazole At the 4th week if not received in the past 6 months                    | <1 (years)     | Do not administer |                            |
|                                                                                            | 1 to 2 (years) | 1/2 tablet        |                            |
|                                                                                            | ≥ 2 (years)    | 1 tablet          |                            |
| Vitamin A
At the 4th week if not received in the past 4 months                   | 6 to 11 months | 100,000 IU        |                            |
|                                                                                            | ≥ 1 month      | 200,000 IU        |                            |

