### 2.1.2. Participants

#### a. Inclusion criteria

To participate in this study, individuals must meet the following criteria:

- Be between 6 and 59 months old;

- To be MAS: PT <-3 Z-score and / or PB <115mm and / or bilateral edema (+, ++);
- Not having any medical complications;
- Have a good result on the appetite test;
- Live in the selected health zone;
- Consent to participate in the study (informed consent);
- Not have other siblings already admitted to the study. When there are several participants in the same siblings, only the first will be included in the EfRAMAS project. The others will be covered according to the national program but will not be part of the study.

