## **f. Organization of the collection**

### ***At UNTA level***

On admission, if a patient meets the study inclusion criteria, the receiving provider explains how the study is going and requests informed consent to include them in the study. If consent is obtained, the nurse assigns an ID to the child that matches the randomization ID. The randomization group is not mentioned. Information on socio-demographic characteristics is collected by IT.

The provider responsible for medically examining the child and taking the anthropometric measurements examines and provides information on the measurements. Anthropometric measurements will be taken according to the PCIMA protocol once a week when the child visits the center until the cured discharge or up to 12 weeks maximum.

- PB will be measured using a PB tape on the left arm halfway between the acromion and the olecranon;
- The weight using a SECA scale depending on whether or not the child can stand up;
- The height will be measured using a wooden measuring board in the supine or upright position depending on whether the child is <24 months or ≥24 months (or ≥ 87 cm) respectively;
- Edemas will be assessed according to their importance (0; + if limited to the feet; and ++ if limited to the legs).

The medical treatment is given to the child according to what is defined in the PCIMA protocol.

Finally, the child receives the amount of RUTF planned for the week as well as health education. It is the same provider in charge of the admission who will ensure the distribution of RUTF and will know who receives the reduced dose according to the IDs of the children. This provider will not follow up on children to keep blind. Each participant receives the quantity of RUTF described in Table 1 (presented above).

All the information on the identifier, the socio-demographic characteristics and the anthropometric measurements are noted in the individual follow-up sheet of the corresponding participant.

**Assessment of psychomotor development:** Depending on the sampling interval, the evaluation of psychomotor development will be carried out on 40% of the sample size, by means of the ASQ 3 score and will include two parts: the execution of the tasks by the child and the filling

of the questionnaire by the guides. For each child, the performance will only last between 10 to 15 minutes. The results of the assessment of psychomotor development are listed in the corresponding item.

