### **3.8. Ancillary and post-test care**

During the study, all participants will benefit from systematic medical care as set out in the PCIMA protocol in force in the DRC.

Up to three months after the recovery of the last participant, close follow-up will be carried out and in the event of a relapse or other medical complications due to the trial, the participants will be taken care of immediately.

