|                                                                                                                                                                                                                                                                                                                                     | Cut                                         | Child's length in cm                                                                                                       | number                                                                                | interval |
|                                                                                                                                                                                                                                                                                                                                     | Weight                                      | Body mass of the child in Kg obtained by weighing                                                                          | number                                                                                | interval |
|                                                                                                                                                                                                                                                                                                                                     | Age                                         | Number of months the child has lived since birth, reported by the caregiver or read on the growth card                     | number                                                                                | interval |
|                                                                                                                                                                                                                                                                                                                                     | PT index                                    | Value obtained by comparing the weight of the child to the median weight of children of his height, obtained using a table | Normal: $\geq -1$ Z score
MAS: $< -3$ Z score
MAM: $\geq -3$ and $< -2$ Z score | Ordinal  |

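### The upper vitamin A age band in Chart 4 is printed in months where years must be meant, so children aged 6–11 months fall under two doses

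*Protocol*

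**What the plan says.** Section 2.1.3 d of the Protocol prescribes the systematic medical treatment for all admitted children, whatever their group, and refers to Chart 4 for the doses. Vitamin A is due "At the 4th week if not received in the past 4 months". The chart then lists two age bands:

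- "6 to 11 months | 100,000 IU"
- "≥ 1 month | 200,000 IU"

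The albendazole entry of the same chart is banded in years: none below 1 year, then "1 to 2 (years) | 1/2 tablet", then a full tablet from 2 years.

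The age criterion in section 2.1.2 a is "Be between 6 and 59 months old". Two other places defer to the national programme for medical care. Section 2.3.1 f states: "The medical treatment is given to the child according to what is defined in the PCIMA protocol". Section 3.8 promises care "as set out in the PCIMA protocol in force in the DRC". Neither repeats the vitamin A bands.

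**The concern.** A dosing table should assign each eligible child exactly one dose. Taken literally, the second vitamin A row starts at an age below the trial's lower limit and so includes the whole trial population. The row above it then has no separate role, and a child of, say, 8 months satisfies both rows.

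What is at stake is the dose that a malnourished infant receives at week 4. Chart 4 is written as an instruction and is applied by routine health-centre staff. ACF supervisors are to ensure strict adherence to the treatment protocol in the UNTAs (section 2.3.1 e), and the safety committee is to evaluate whether the protocol is strictly applied (section 2.4.1). Read against Chart 4 as printed, neither check could tell the lower dose from the double dose as the correct one for a child under 1 year. The trial's statistical conclusions are not at stake.

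**Working it through.** There is no figure of the plan to reproduce. The check compares the age bands with each other and with the eligible range.

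**Inputs**

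- Eligible age: 6 to 59 months (section 2.1.2 a).
- Lower vitamin A band: 6 to 11 months, 100,000 IU (Chart 4).
- Upper vitamin A band as printed: 1 month or older, 200,000 IU (Chart 4).
- Ages are counted in completed months, as in Annex 8, which defines age as "Number of months the child has lived since birth, reported by the caregiver or read on the growth card".

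**As printed**

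- Eligible months of age: 59 − 6 + 1 = 54.
- Covered by the lower band: 11 − 6 + 1 = 6.
- Covered by the upper band within eligibility: 54 of 54, because every eligible age exceeds 1 month.
- Covered by both bands: 6 months of age (6–11).
- Ratio of the two doses in the overlap: 200,000 / 100,000 = 2.

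**With the upper band at 12 months or older**

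- Covered by the upper band within eligibility: 59 − 12 + 1 = 48.
- Covered by both bands: 0.
- Covered by either band: 6 + 48 = 54 of 54, so there is no gap.

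**Which reading is intended.** Three features point to 1 year. The band above ends at 11 months, so the next one naturally starts at 12. The albendazole rows of the same chart break at 1 year. The numeral 1 fits if only the unit word is wrong. A threshold of 12 months also makes the two rows fit the eligible range exactly.

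**Whether another section settles it.** Section 1.1 mentions vitamin A as part of care but gives no dose. Sections 2.3.1 f and 3.8 point to the national protocol without restating the bands. The contradiction therefore stands within this document.

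**How many children.** Only those aged 6–11 months who reach week 4 without vitamin A in the preceding 4 months are concerned. The Protocol does not allow that number to be computed, and none is assumed here.

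**The case against.** The best case for leaving this alone has four parts.

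- **Origin.** The English text shows many signs of translation from French. One is in Chart 6 of the same section, where a fraction of three quarters comes out in a garbled form. The version used at the sites may be correct. This is plausible and cannot be settled from the text. It does not change the remedy, because the sponsor can easily look.
- **Other sources of the dose.** Section 2.1.3 says that care follows the national protocol and that only the RUTF dose differs between arms. Section 2.3.1 f defers to PCIMA for medical treatment, and staff are trained on it. This lowers the practical risk. It does not remove it: teams are also trained on the research protocol (section 2.3.1 b), providers who leave are replaced by others trained by the research team (section 2.1.3 c), and Chart 4 is worded as a direction.
- **The specific row wins.** A nurse treating an 8-month-old sees a row naming that age exactly and would probably use it. That is fair. It still means relying on the reader's judgement to resolve a contradiction in a dosing table.
- **No demonstrated harm, no effect on the comparison.** The Protocol shows only that the printed doses differ twofold. It says nothing about the consequences of the higher dose under 1 year, and no claim about them is made here. Both arms receive the same treatment, so the comparison is untouched.

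These points limit the weight of the concern and show that it is an erratum rather than a fault of design. None of them corrects the printed cell.

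**Conclusion.** The concern holds. As printed, Chart 4 assigns two vitamin A doses, differing by a factor of two, to children aged 6–11 months, who make up 6 of the 54 eligible months of age. That the cell was meant to read 1 year is an inference, though a strong one. Whether the same slip is in the copies held at the sites is unknown.

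This is a correction to a dosing instruction that should be made. It has no bearing on the non-inferiority margin, the sample size or the analysis.

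**What to change.** In Chart 4, change the upper vitamin A band to 12 months or older, after checking it against the national protocol (reference 12). Stating it in months matches the row above and the age variable in Annex 8. Check the version held at the 14 UNTAs and any training material that reproduces the chart, and correct these if they carry the same entry.

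The cost is one table cell and a short check of derived material, recorded under the amendment procedure in section 3.3. Nothing in the design, the sample size or the analysis has to change.

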#### e. Nutritional measurement and monitoring

Chart 5 : Nutritional monitoring and taking measures

| Observations                          | Frequencies                                                    |
|---------------------------------------|----------------------------------------------------------------|
| MUAC measurement                      | Every week                                                     |
| Weight measurement                    | Every week                                                     |
| Search for edema                      | Every week                                                     |
| Appetite test                         | Every week                                                     |
| Temperature measurement               | Every week                                                     |
| Complete clinical examination         | Every week                                                     |
| Size measurement                      | Every week                                                     |
| Calculation of the PT index (z-score) | Every week                                                     |
| Nutrition education                   | Every week                                                     |
| Assessment of RUTF consumption        | Every week                                                     |
| Home visit                            | Depending on the case: if absence or no answer                 |
| Vaccination                           | Complete the vaccination schedule at the 4th week              |
| Assessment of psychomotor development | On admission, discharge, and 6 months after recovery           |
| Vaccination                           | Complete the vaccination schedule at the 4th week of follow-up |

At each visit (week), the mothers / carers of the children benefit from a nutritional equation session, the essential points of which are:

- RUTF is a medicine intended exclusively for the management of children with severe malnutrition and therefore it should not be shared or sold;

- Do not force the child to eat. One sachet of RUTF can be consumed in several meals;
- The child should always be given drinking water when taking RUTF;
- For children who are breastfeeding, breastfeed the child before giving RUTF;
- RUTF meets the daily nutritional needs of the child, always give it before other foods (for children who are not under breastfeeding);
- The accompanying person should wash their child's hands and face with soap before giving RUTF;
- Specify to the accompanying person the amount of RUTF that their child must eat per day;
- The treatment must be respected: for a good recovery, the child must be consulted every week for a minimum period of 1 month and a half;
- The accompanying person must return the empty sachets of RUTF and the sachets not consumed to the UNTA
- caregivers and family members should not consume RUTF instead of the child, even for reasons of breastfeeding or feeding other children.

Chart 6 : Appraisal of the appetite test based on the proportion of dough consumed

| Body weight
(kg) | RUTF - paste in sachet
(Proportion of a whole bag 92g) |            |       |
|---------------------|-----------------------------------------------------------|------------|-------|
|                     | Weak                                                      | Average    | Good  |
| <4                  | <1/8                                                      | 1/8 - 1/4  | > 1/4 |
| 4 to 6.9            | <1/4                                                      | 1/4 - 1/3  | > 1/3 |
| 7 to 9.9            | <1/3                                                      | 1/3 - 1/2  | > 1/2 |
| 10 to 14.9          | <1/2                                                      | 1/2 - 3/4  | > 3/4 |
| 15 to 29            | <3/4                                                      | 04/03 to 1 | > 1   |
| > 30                | <1                                                        | > 1        |       |

To have good results in the appetite test, the following measures must be observed:

- Wash your child's hands and face and hands before giving RUTF;
- Obtain a cup of drinking water;
- Find a comfortable place;
- Do not force the child to eat;
- Check if the child has eaten in the last 30 minutes.

#### 2.1.4.Results

##### a. Main result

The main outcome of this study will be the velocity of weight gain for each participant in the two study groups (control and intervention group). The acceptable weight gain is 5 g / kg / day for each participant regardless of the group to which he belongs. This weight gain is an average calculated between the gain on admission and on discharge for all the children admitted to the study (intention to treat) and then only for those who are declared cured (per protocol).

To conclude that there is no inferiority, it is assumed that the reduced dose will not be less than the standard dose if the difference in weight gain is less than 0.5 g / kg / day. Therefore, participants in the intervention group should not show a weight gain <4.5 g / kg / day to conclude that the reduced dose of RUTF was not inferior.

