##### b. Additional results

The additional results expected in this study, in the two groups (control and intervention), are:

- **The duration of the edema melting:** calculated in number of days, this indicator corresponds to the time taken for the lower limbs of SAM children to return to their normal volume. The expected result is the onset of melting of the edemas within the first 14 days after admission and their complete disappearance after 21 days of treatment.
- **The length of stay:** calculated in number of days, this indicator corresponds to the time elapsed between admission and discharge ( $PB \geq 12.5\text{cm}$  and / or  $PT \geq -3$  Z score and / or edema melt). The maximum length of stay is 12 weeks or 3 months(12).
- **The cure rate:** A child will be considered cured if he meets the cure criteria according to his admission category: A  $PT \text{ index} \geq -1.5$  or  $PB \geq 125 \text{ mm}$  during two consecutive visits and no edema during two visits (2 consecutive weeks).
- **The dropout rate:** it is the proportion of children confirmed alive who missed two successive visits. The abandonment is confirmed once after the visit of the RECO which confirms that the child is alive despite his 2 absences during the weekly visits. Children who have abandoned will be followed up to 3 months after the abandonment. For children who can be found, offer the caregivers a small snack at the single appointment 3 months after abandonment to take the anthropometric measurements.
- **Death rate :** the proportion of children randomized to the study who died during the intervention at any time.
- **Cost savings** (average cost saved and cost saved per child treated): this involves comparing the cost of treatment for children in care and declared cured in the two groups. We will use a societal perspective including the direct costs of drugs and RUTF

(purchase, transport, transport and storage) to assess the cost for each child, the HR costs involved in the care, the non-medical costs (food and transport. beneficiaries), indirect costs (loss of productivity).

- The growth velocity of the anthropometric variables and indices: it will be a question of evaluating the prevalence of stunting, underweight of the children included in the study in the two groups at the end of the treatment.

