### **2.3.3. Statistical analyzes**

For the quantitative part of the study, the data will be summarized in Mean and Standard Deviation if they are normally distributed (normality test) for continuous variables and in absolute and relative frequencies for categorical variables.

The t-test and the chi-square test will be used respectively to compare the means and the proportions of the socio-demographic characteristics at admission for the quantitative and qualitative variables.

Linear regression analyzes will be used to determine the significant differences between the 2 groups of children for the quantitative variables.

Binary logistic regression analyzes will be used to determine the significant differences between the 2 groups of children for the binomial qualitative variables (2 response modalities).

Multinomial logistic regression analyzes will be used to determine the significant differences between the 2 groups of children for the multinomial qualitative variables (3 or more modalities).

All analyzes will be done in an adjusted and unadjusted model and a difference is statistically significant when the P-value is less than 0.05.

The results will be analyzed using statistical software, in this case STATA, version 17.

The main analyzes will be done by intention to treat (ITT) and per protocol for the main result, in this case, the speed of weight gain. The other secondary results will be analyzed only by intention to treat (ITT).

For the DPM, a score will be assigned to the participant and the sum will constitute the total score for each participant per domain.

For focus group data, after transcription of the recordings into Word 2019, thematic analysis will be done using Excel tables (matrix) or Nvivo® software.

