##### **Duration and pace of the assessment**

For each participant, the test lasts between 10 to 15 minutes maximum. Each child will undergo three assessments, one on admission, one at discharge in the third month (exit from treatment for children declared cured) and one in the sixth month.

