|                                                                                                                                                                                                                                                                                                                                     | Presence of edema                           | Increased volumes of the lower limbs taking the bucket                                                                     | Absent: normal volume
+ or ++                                                      | nominal  |
|                                                                                                                                                                                                                                                                                                                                     | Rate of weight gain in children             | Ratio of the difference in weight between discharge and admission / initial weight / duration of treatment (g / kg / d)    | number                                                                                | interval |
|                                                                                                                                                                                                                                                                                                                                     | SAM proportion without complications.       | Ratio of all uncomplicated SAM children to the total of AD children received during recruitment                            | %                                                                                     | interval |
|                                                                                                                                                                                                                                                                                                                                     | Sex                                         | Child gender                                                                                                               | Male
Feminine                                                                      | nominal  |

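### The per-protocol set for the primary outcome is the children declared cured, so that analysis selects on a result tied to weight gain, and no rule says whether it or ITT decides

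*Protocol*

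**What the plan says.** Section 2.1.4 a (Main result) computes mean weight gain "for all the children admitted to the study (intention to treat) and then only for those who are declared cured (per protocol". Section 2.3.3 gives both sets main status: "The main analyzes will be done by intention to treat (ITT) and per protocol for the main result". The protocol has no definition of per protocol based on adherence, and no rule for the case where the two sets disagree.

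The outcome and the selection criterion overlap:
- Annex 8 defines velocity as "Ratio of the difference in weight between discharge and admission / initial weight / duration of treatment (g / kg / d".
- Section 2.1.4 b defines cure by anthropometric targets: "A child will be considered cured if he meets the cure criteria according to his admission category". These are a weight-for-height or MUAC threshold at two consecutive visits, with no edema.
- Chart 3 in section 2.1.3 b lists non-responders as "Children who do not recover after 12 weeks of treatment".
- Section 2.1.3 a counts weight loss or stagnation among the treatment-failure criteria that lead to transfer.

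Cured-only wording also appears for two secondary outcomes. On costs, section 2.1.4 b says "this involves comparing the cost of treatment for children in care and declared cured in the two groups". On the exit psychomotor test, Annex 3 (duration and pace of the assessment) specifies "exit from treatment for children declared cured". Section 2.3.3, however, states: "The other secondary results will be analyzed only by intention to treat (ITT".

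**The concern.** A per-protocol set should contain the children who were treated as the protocol intended. In a non-inferiority trial it is there to show that a small difference is not merely the product of poor adherence diluting the contrast. Here membership depends on how the child did. A child who took the allocated ration and did not recover in 12 weeks is left out, and so is a transferred child who does not return and recover. A cured child who was given the other arm's ration stays in.

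If the reduced dose slows weight gain, more of its slow gainers fall short of cure and drop out of the comparison, and the two arms look closer than they are. At stake is the error rate of one of the two analyses on which the primary conclusion may rest. With no rule on which set decides, a favourable cured-only result could be put forward as the trial's finding.

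**Working it through.** **Inputs from the protocol.** Mean 5 and SD 2.6 g/kg/day, margin 0.5, expected difference 0, z = 1.64 (one-sided 5%), power 80%, 335 per group (section 2.1.6). 500 per arm (Annex 5, study population).

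**Assumed inputs.** Control cure rate 75% or 85%; Annex 4 says only that cure often exceeds 75%. Correlation rho between velocity and the score that determines cure: 0.3 to 1.0. The protocol fixes neither.

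**The plan's own figure.** n = (1.645 + 0.842)² × 2 × 2.6² / 0.5² = 334.4, so 335 per group. This reproduces. (The rounded values 1.64 and 0.84 give 332.6.)

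**Model.** The true loss is exactly at the margin: control velocity is N(5, 2.6), reduced-dose velocity N(4.5, 2.6). A child is cured if a latent score, correlated rho with velocity, exceeds a threshold k set to give the control cure rate. On the standard scale the cut-off is a = k in control and a = k + rho × 0.5/2.6 in the reduced arm. With λ(a) = φ(a)/(1 − Φ(a)):
- mean among the cured = arm mean + 2.6 × rho × λ
- variance among the cured = 2.6² × [1 − rho² × λ × (λ − a)]
- apparent loss d = 0.5 − 2.6 × rho × (λ reduced − λ control)
- chance of declaring non-inferiority = Φ((0.5 − d)/SE − 1.645)

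Without selection d = 0.5, and the chance is Φ(−1.645) = 5%.

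**Worked case: rho 0.7, control cure 75%, 500 per arm.**
1. k = −0.6745. The reduced-arm cut-off is −0.6745 + 0.1346 = −0.5399, so 70.5% are cured there.
2. λ = 0.4237 (control) and 0.4889 (reduced).
3. d = 0.5 − 1.82 × 0.0652 = 0.38.
4. SE = √(5.219/375 + 5.094/352.7) = 0.168.
5. Φ(0.119/0.168 − 1.645) = about 17%.

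At 335 per arm the same case gives 14.3%; a simulation of 20,000 trials gave 14.1%.

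**Second scenario.** Section 2.1.6 allows 20% dropout and Chart 3 calls non-response very rare. So let 15-20% of children default independently of gain and 5% of the remaining controls fail through the latent score. Overall control cure is then 0.85 × 0.95 = 81% to 0.80 × 0.95 = 76%, inside the same range.

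**Results, 500 per arm: apparent loss (true 0.5); false non-inferiority in the cured-only analysis (nominal 5%).**

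| rho | All non-cure velocity-linked, cure 75% | Same, cure 85% | 15-20% unrelated default, 5% linked failure |
|---|---|---|---|
| 0.3 | 0.48; 6.3% | 0.48; 6.0% | 0.49; 5.5% |
| 0.5 | 0.44; 9.5% | 0.45; 8.5% | 0.475; 6.6% |
| 0.7 | 0.38; 17% | 0.41; 14% | 0.45; 9% |
| 1.0 (bound) | 0.25; 55% | 0.31; 39% | 0.39; 16% |

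With a true difference of 0 both arms are selected identically in this model, and no bias arises.

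**Secondary populations, side by side.**
- Costs: section 2.1.4 b takes cured children. Annex 5 takes all enrolled children (study population; sample size) and includes inpatient costs of complications.
- Exit psychomotor test: Annex 3 and section 2.3.1 f tie it to cure. Chart 5 and the data collection plan in section 2.3.1 b place it at discharge with no cure condition.

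**The case against.** The strongest reply is that ITT in all admitted children is also a main analysis, is named first and does not select on cure. That stands. A reader might infer that the trial as a whole is biased towards non-inferiority, and the protocol does not support that. If both sets had to agree, the joint error could not exceed the ITT error, 5% in this model. But the protocol does not say that both must agree.

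Three other strong readings also fail:
- **That every transfer and treatment failure is removed.** Section 2.1.3 says transferred children return to their group, Chart 3 marks treatment failure as a temporary discharge, and Annex 5 foresees children who return and complete treatment successfully. Only those who never reach cure are lost. For the same reason, cured-only costs would not leave out every hospital stay.
- **That the error rate reaches 39-55%.** This needs a correlation of 1.0 and every non-cure driven by velocity. Cure also depends on the starting deficit and on edema, and much non-cure may be default. These figures are only an upper bound.
- **That adherence plays no part at all.** Children who abandon, withdraw or are lost will generally not be declared cured, so the set does exclude much gross non-adherence. It still drops adherent non-responders and keeps cured children given the wrong ration.

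It might also be said that analysis sets belong in a statistical analysis plan. Here the protocol itself fixes the definition.

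**Conclusion.** The definition is wrong as written: it conditions a main analysis of the primary outcome on a post-randomisation result tied to that outcome. The direction of the bias is firm whenever cure tracks weight gain and the reduced dose slows it. Its size is modest to moderate. For a true loss at the margin, the cured-only analysis falsely declares non-inferiority about 6%, 9% or 14-17% of the time at correlations of 0.3, 0.5 and 0.7 if all non-cure follows velocity, and about 5.5%, 6.6% or 9% if most of it is unrelated default. These figures rest on assumed cure rates and correlations. The missing decision rule is what lets this bias reach the primary conclusion. The cost and psychomotor populations are separate inconsistencies and do not affect the non-inferiority error.

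**What to change.** 1. In sections 2.1.4 a and 2.3.3, define per protocol by conduct, regardless of cure: eligible at admission, allocated ration received at a pre-set share of attended visits, no crossover. Fix the share before any data by arm are seen.
2. Keep velocity among cured children as a descriptive subgroup under that name.
3. State that non-inferiority requires both ITT and the redefined per-protocol set.
4. Reconcile the cost population in section 2.1.4 b with Annex 5. Reconcile the exit psychomotor population in Annex 3 and section 2.3.1 f with Chart 5, the data collection plan and the ITT statement in section 2.3.3.

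The cost is mainly wording. RUTF distribution and consumption are already scheduled weekly (Chart 5 and the data collection plan), so the adherence data should exist. If the psychomotor test is aligned to discharge, a few more exit assessments would be needed in the sub-sample. One limit remains: a conduct-based set still selects after randomisation, so it supports the ITT analysis and does not replace it.
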